## **Part 1b: Static fitting, dynamic fitting and prosthetic alignment**

Subjects will return for fitting of the definitive sockets/prostheses by the study prosthetist. The additional prostheses will initially be bench aligned, based on manufacturer's specifications, for a static fitting on the subject. After successful static fitting is achieved, the dynamic alignment of each prosthesis will occur. The subject will ambulate using each of the duplicate prostheses and adjustments will be made to the alignment, as needed, to achieve an optimal gait pattern, as determined by each subject, site prosthetist and/or research team. Dynamic fitting may take multiple visits, and subjects will progress to the next part of the protocol after an appropriate dynamic alignment has been established.

### *Device Specific Training to Meet a Minimum Standard of Performance*

After appropriate fit and alignment of each prosthetic device has been established, all subjects will undergo device specific training by a qualified clinician using each foot to meet a minimum standard of functional performance. The minimum standard will be defined using the mobility section of the FIM with each prostheses. The participant must score a minimum of "modified independence" to advance in the study (detailed in the Intervention Plan). If the participant fails to achieve this outcome, gait training/rehabilitation to enhance the participant's use of their prosthetic foot will be provided until they are able to meet the minimum standard of performance (further outlined in the Intervention Plan). The process of device specific training may take multiple visits. Part 2 of the protocol will begin when a subject meets the minimum standard of performance.

### **Specific Aim 1:** Assessment of function using ESR, Articulating ESR and Active Plantarflexion ESR ankle-foot prostheses

Parts 2-4 of the study will address Specific Aim 1. Part 2 will begin with issuing the first of the 3 well-fitting prostheses according to the randomization schedule, including a 1 week acclimation period. At the conclusion of this acclimation period, a battery of outcome measures and surveys (outlined below) will be collected. For Part 3, the subject will receive the second prosthesis according to the established randomization schedule and the initial prosthesis will be returned to the study prosthetist. The subject will again have a one week acclimation period followed by the collection of the same battery of outcome measures and surveys. The third prosthesis will be issued during part 4, and the second prosthesis will be returned to the study prosthetist. The subject will receive the same one week acclimation followed by the battery of outcome measures and surveys.

## **Outcome Measures**

The battery of functional outcome measures and surveys/guided interviews delivered after each acclimation period is delivered by a local researcher. Functional outcome measures include the 6-Min Walk, TUG, 4SST,

Amputee Mobility Predictor (AmpPRO), stair assessment index (SAI), and hill assessment index (HAI). Surveys/guided interview include Prosthetic Evaluation Questionnaire (PEQ), Short Form-12 (SF-12), and Orthotics and Prosthetics User Survey (OPUS).

- **6-Min Walk:** This test measures the distance an individual can walk in 6 minutes without help or encouragement. The 6-minute walk test is valid and reliable metric. It correlates with physical function and functional capacity (26, 27). This test has been proven to have good inter-rater and intra-rater reliability in transtibial amputees (26).
- **TUG:** The TUG measures the time taken by an individual to stand up from a standard arm chair, walk a distance of 10 feet, turn, walk back to the chair, and sit down. The TUG is both reliable and valid in a population with unilateral transtibial and transfemoral amputation (28). Additionally, the TUG has also been used as a measure to determine risk of falling (29, 30). This measure has also shown to correlate well with other measures of physical functioning (31).
- **4SST:** The 4SST is a higher order complex task assessing dynamic balance (32, 33).
- **AmpPRO:** The AmpPRO is a 21-item instrument designed to measure basic prosthetic mobility of individuals with lower extremity amputation (34).
- **HAI:** The HAI is a rated qualitative scale on how an individual with lower limb amputation negotiates up and down an incline (35).
- **SAI:** The SAI is a rated qualitative scale for stair negotiation (35).
- **PEQ:** The PEQ is self-report visual analog scale-style questionnaire for persons with lower limb amputations who use a prosthesis. It is used to evaluate the prosthesis and life with the prosthesis. It consists of 82 items with nine functional domain scales including ambulation, residual limb health, utility, appearance, sounds, frustration, perceived response, social burden and well-being. The PEQ also contains items beyond the subscales including satisfaction, pain, transfers, prosthetic care, self-efficacy, and importance (36).
  - **PEQ-Addendum:** This is an addendum to the PEQ, and it is a self-reporting measure to assess any stumbles and/or falls that occur during study protocol participation.
- **SF-12:** The SF-12 can be used to measure the relationship between physical and mental health functioning and the social determinants of health (37).
- **OPUS:** OPUS is a set of self-report instruments that assess functional status, quality of life, and satisfaction with devices and services that can be used in an orthotics and prosthetics clinic. It can be used with patients with varying levels of lower limb function, quality of life, and satisfaction with devices and services (38).

## **Research Monitoring**

The Research Monitor, [name], OT, at the VA NY Harbor Healthcare System is responsible for overseeing the safety of the research and reporting findings to the IRB. The Research Monitor will review all unanticipated problems involving risks to subjects or others associated with the protocol and provide an independent report of the event to the IRB. Reports of the progress of the study will be completed by the Research Monitor and submitted to the IRB and HRPO (Human Research Protection Office at the DoD), as needed. This includes an analysis of any stumbles and/or falls that occur with any of the enrolled research subjects throughout their participation in the protocol activities. The Research Monitor will discuss the research protocol with the investigators; shall have authority to stop the research protocol in progress, remove individual human subjects from a research protocol, and take whatever steps are necessary to protect the safety and well-being of human subjects until the IRB can assess the monitor's report; and shall have the responsibility to promptly report their observations and findings to the IRB official and the HRPO.

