#### Part 5: Step Activity Monitoring

Specific Aim 3 will be addressed with Part 5 of this protocol. After completion of Part 2-4, subjects will receive all three prosthetic limbs for use for a period of 30 days. All three limbs will be fitted with a Modus Health step activity monitor (SAM), which is a research-grade instrument for long-term assessment of ambulatory activity during day-to-day life. Subjects will also use an activity log to document their daily activities to allow for correlation between prosthesis used and activity. Subjects are free to use each prosthesis as they chose. Subject prosthetic preference will be based upon total activity time for each prosthesis.

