#### SA3 Data Analysis:

Daily step counts and level of activity (low, medium, high) will be collected from each SAM attached to each prosthesis, and daily activity logs will be analyzed to determine which devices were used for specific activities (i.e. everyday use, leisure, housework). Together, this will help determine rationale for patient preference of prosthesis. Additionally these findings will be correlated with previous outcome measures from Parts 2-4.

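### The only named stumble and fall questionnaire is scheduled before the 30-day Part 5, and no stumble or fall collection is stated for Part 5 itself

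*Protocol*

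**What the plan says.** **Purpose.** Under Research Monitoring, the Research Monitor's progress reports include "an analysis of any stumbles and/or falls that occur with any of the enrolled research subjects throughout their participation" in the study's activities. The same section gives the Monitor authority to stop the research or withdraw a subject, and a separate duty to review unanticipated problems.

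**Instrument.** Under Outcome Measures, the PEQ-Addendum is the self-report form for stumbles and falls. Its described scope is events at any time in the study. It is listed beneath the PEQ, within a battery timed as follows: "The battery of functional outcome measures and surveys/guided interviews delivered after each acclimation period is delivered by a local researcher".

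**Schedule.** The Specific Aim 1 assessment section places one acclimation period in each of Parts 2, 3 and 4. In its words these are "including a 1 week acclimation period", then "The subject will again have a one week acclimation period", then "The subject will receive the same one week acclimation". In each Part the battery follows.

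**Part 5.** "After completion of Part 2-4, subjects will receive all three prosthetic limbs for use for a period of 30 days". Subjects choose freely which limb to wear. Under SA3 Data Analysis, "Daily step counts and level of activity (low, medium, high) will be collected from each SAM attached to each prosthesis", and the activity logs show which device was used for which kind of activity. Neither section mentions the PEQ-Addendum, a fall item or a closing assessment.

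**The concern.** The purpose and the schedule do not meet. The Monitor's analysis is meant to run across the whole of participation, and so is the questionnaire that would feed it. Yet the last stated use of that questionnaire is at the end of Part 4. A recall form completed then cannot record what happens in the 30 days that follow.

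Part 5 matters for safety because it is the only home period in which a subject holds all three ankle types and moves between them at will. In Parts 2 to 4 the previous limb is returned when the next one is issued. If stumbles and minor falls in Part 5 are not recorded at the time, they cannot be reliably recovered later. The person with authority to stop the study would then be working from an incomplete fall record.

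A secondary point concerns interpretation. Part 5 preference is measured by total activity time on each limb and is the outcome of the prediction model. Without fall data, a limb set aside after a fall looks the same as one that was simply not liked. This is a possibility only, and the point does not depend on it.

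**Working it through.** The protocol gives no exposure share, fall rate or fall-based sample size, so there is no figure of its own to reproduce. The check sets the schedule against the stated purpose and then sizes the gap.

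**Step 1: coverage by study part**

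| Part | Home use stated | Stumble/fall collection stated |
|---|---|---|
| 2 | 1 week, first limb | PEQ-Addendum in the battery afterwards |
| 3 | 1 week, second limb | PEQ-Addendum in the battery afterwards |
| 4 | 1 week, third limb | PEQ-Addendum in the battery afterwards |
| 5 | 30 days, all three limbs | none stated |

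**Step 2: share of stated home-use days**

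Inputs: three acclimation periods of 7 days (Specific Aim 1 assessment section) and 30 days (Part 5 section).

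- Parts 2 to 4: 3 × 7 = 21 days
- Total: 21 + 30 = 51 days
- Part 5 share: 30 / 51 = 58.8%
- Share with a scheduled questionnaire: 21 / 51 = 41.2%

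For the planned 120 subjects, if all complete:

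- Parts 2 to 4: 120 × 21 = 2,520 subject-days
- Part 5: 120 × 30 = 3,600 subject-days
- Total: 6,120 subject-days

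**Step 3: sensitivity to visit timing**

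The protocol does not say how many days pass between the end of an acclimation week and the testing and exchange visit. With g extra days per period (an assumption), the share is 30 / (3 × (7 + g) + 30):

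| g (days) | Calculation | Part 5 share |
|---|---|---|
| 0 | 30 / 51 | 58.8% |
| 1 | 30 / 54 | 55.6% |
| 3 | 30 / 60 | 50.0% |
| 7 | 30 / 72 | 41.7% |

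Part 5 is more than half of home use only if g is below 3 days. At every value shown it is the longest single home period: 30 days against at most 7 + 7 = 14. Any home use during Part 1b fitting and training is not stated and is not counted.

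**Step 4: effect of the fix**

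A questionnaire at the end of Part 5 raises the scheduled coverage from 21 of 51 days to 51 of 51.

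**The case against.** A reader might infer that falls in Part 5 are excluded from the Monitor's analysis, or that no fall in Part 5 could come to light. The documents do not support either reading, and the case against them has several parts.

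- **No text excludes Part 5.** The scope of the PEQ-Addendum and the scope of the Monitor's analysis both take in the whole of participation, and they agree with each other. What is absent is a stated time or method of collection. This stands, and it fixes the form of the point: the schedule falls short of an intention that is itself sound.
- **Another route stays open.** The Monitor reviews unanticipated problems with no limit to visits or study parts, and all sites confer monthly. A fall with injury could well arrive this way. This stands too. However, the text gives no prompt or form for this route in Part 5, and a stumble or harmless fall may never be raised as an unanticipated problem. The protocol also lists the fall analysis separately from that review.
- **Some material is not visible.** The subject timeline (Figure 6) is not shown, and the activity log form is not reproduced. A closing assessment or a fall entry in the log cannot be ruled out. This limits confidence, although the written descriptions of the battery and of Part 5 mention neither.
- **The size depends on timing, and no fall count can be given.** The 59% needs acclimation periods of exactly 7 days, so a reader should not conclude that most home exposure is certainly uncovered. The documents give no fall rate, so any number of missed falls would rest wholly on an outside assumption.
- **No inference depends on falls.** No hypothesis concerns them and the Power Analysis does not use them. This stands and lowers the severity.

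The objection that a statistical analysis plan may settle the matter does not stand. When events are recorded is a matter of data collection, and no later plan can analyse what was not recorded.

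**Conclusion.** The point holds as a gap between a stated safety purpose and the schedule meant to serve it. As written, stumbles and falls without injury have no stated capture route in Part 5, so the Monitor's fall analysis would be incomplete for that period.

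Part 5 accounts for about 59% of stated home-use days on exact 7-day acclimations, and about 42% to 56% if each runs 1 to 7 days longer. The conclusion does not depend on where in that range the truth lies, nor on any fall rate. It does assume that the missing timeline figure and the log form add no collection point that the text omits, so confidence is moderate.

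Severity is should-fix. The consequence is less complete safety data; the planned tests and the sample size are untouched.

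**What to change.** Three changes, to be in place before subjects enter Part 5:

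1. Repeat the PEQ-Addendum at the end of Part 5, with a recall window covering the 30 days.
2. Add one line to the daily activity log already used in Part 5: stumble or fall (yes/no), prosthesis worn, injury (yes/no). This dates the event and ties it to a limb, which a single recall form after 30 days of switching may not do.
3. State under Research Monitoring that the fall analysis covers Parts 2 to 5. Word it so that events during Part 1b fitting and training, which the present wording already takes in, are not dropped.

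If the timeline figure or the log form already provides for this, it is enough to say so in the Outcome Measures and Part 5 sections.

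The cost is a protocol amendment, one log line and one short existing questionnaire, which could be completed when the monitors and logs are returned. The extra burden on subjects is slight.

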## **SAI: Data and Statistical Analysis**

*Hypothesis 1.1 Subjects will prefer articulating ESR and active plantar flexion ESR ankle-foot units over the non-articulating ESR option for community mobility, particularly for those that regularly negotiate inclines and declines.* Preference will be demonstrated in the PEQ mobility questions. Across the study population, outcomes will be assessed with descriptive statistics (i.e. means and standard errors) and compared between

each intervention prosthesis. Inferential statistics for ordinal data (SAI, HAI) will be conducted with a repeated measures Friedman test ( $\alpha=.05$ ) and a Dunn post hoc test at a 95% confidence interval. To analyze the bivariate relationships between the factors of interest and the outcome measures (SAI, HAI), t-tests will be performed.

*Hypothesis 1.2 Active plantar-flexion ESR feet will result in better performance metrics for mobility based outcome measures.* For each functional outcome measures (6-min walk, TUG, AmpPRO, SAI and HAI) we will perform a repeated-measures analysis of variance (ANOVA) to compare the 3 testing conditions. When the ANOVA reveals significant differences ( $p < 0.05$ ), we will apply pairwise comparisons using related pairs t-tests to identify the source of differences ( $p < 0.05$ ). We will compute the difference between a given pair of sessions for the subject groups and determine the mean difference for subject groups.

*Hypothesis 1.3 Subjects will have decreased pain scores as determined by the visual analog scale (VAS) within the Prosthetic Evaluation Questionnaire when using the active plantarflexion ESR ankle-foot prosthesis*

The PEQ contains a VAS for pain within the evaluation. Spearman correlations, a statistical measure of the strength of a monotonic relationship between paired data will be calculated to correlate data between pain and functional outcome values across the 3 groups. Linear mixed-effects models will be used to identify statistically significant differences in pain scores and functional outcome variables. In the case of significance, pair-wise comparisons will be tested for significance using linear contrasts with Tukey's Honestly Significant Difference or applying Bonferroni's correction. Finally, stepwise multiple regression will be performed with VAS pain as the dependent variable. The independent variables will be comprised of functional parameters and condition (foot type). Significance will be set at  $p < 0.05$ . Variables will be eliminated if  $p$  is  $> 0.1$ .

*Hypothesis 1.4 There will be no significant differences in functional outcome measures within all tested non-articulating ESR feet regardless of specific foot assigned.*

*Hypothesis 1.5 There will be no significant differences in functional outcomes within all articulating ESR feet tested regardless of specific foot assigned.*

Functional measures will be analyzed by multilevel (site) repeated measures analysis of variance. Because order of prosthesis will be randomized, there should be no order effect. However, order will be included in the initial analysis to test this assumption. When the ANOVA reveals significant differences ( $p < 0.05$ ), we will apply pairwise comparisons using related pairs t-tests to identify the source of differences ( $p < 0.05$ ).

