#### Power Analysis:

| Site                                                | n   | n for subset |
|-----------------------------------------------------|------------|---------------------|
| VA New York Harbor Healthcare System (NYC)          | 30         | 15                  |
| Walter Reed National Military Medical Center (D.C.) | 30         | 15                  |
| VA Puget Sound Healthcare System (Seattle)          | 30         | 0                   |
| James J. Peters VA Medical Center (Tampa)           | 30         | 0                   |
| TOTAL                                        | 120 | 30           |

Figure 7. Total Subjects per site to be seen over the course of 3 year period

#### Specific Aim 1

Functional measures will be analyzed by multilevel (site) repeated measures analysis of variance. Because order of prosthesis will be randomized, there should be no order effect. However, order will be included in the initial analysis to test this assumption. Assuming an alpha error rate of 5% and within-group standard deviation of 5, 120 subjects will provide over 98% power to detect a 3 unit difference between at least two of the ESR groups for each of the functional measures.

### Specific Aim 2

Kinematic and kinetic measures will be analyzed by multilevel (site) repeated measures analysis of variance. Because order of prosthesis will be randomized, there should be no order effect. However, order will be included in the initial analysis to test this assumption. Assuming an alpha error rate of 5% and within-group standard deviation of 10, 30 subjects will provide 72% power to detect a 6-unit difference between at least two of the ESR groups for each of the measures.

### Specific Aim 3

This analysis will be performed using paired t-test to determine correlations between prosthesis chosen as per SAM data and which functional outcome measures are indicative of that choice. Additionally pair t-test will be performed between kinematic and kinetic data to again correlate with the prosthetic choice of the subject as demonstrated through the SAM data. Finally all SAM data will be evaluated against the activity journal to determine the roll of a specific activity goal and a specific prosthesis.

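### The Dunn post hoc test named for the stair and hill ratings is needlessly conservative when ratings tie, so the Hypothesis 1.1 analysis can be significant overall yet identify no foot pair

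*Protocol*

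**What the plan says.** The protocol section headed *SAI: Data and Statistical Analysis* states under Hypothesis 1.1: "Inferential statistics for ordinal data (SAI, HAI) will be conducted with a repeated measures Friedman test" at alpha 0.05, followed by "a Dunn post hoc test at a 95% confidence interval". It does not say which form of Dunn's test is meant or how ties are treated.

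*Outcome Measures* describes the two scales as ratings: "The SAI is a rated qualitative scale for stair negotiation" and "The HAI is a rated qualitative scale on how an individual with lower limb amputation negotiates up and down an incline". It gives no number of levels, distribution or expected tie rate.

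The data are paired. The *Specific Aim 1* assessment section starts with "issuing the first of the 3 well-fitting prostheses according to the randomization schedule" and repeats the same battery after the second and third foot. Before testing, each subject must reach a functional floor with every foot: "The minimum standard will be defined using the mobility section of the FIM with each prostheses".

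Under Hypothesis 1.2 the same section lists SAI and HAI again, this time for repeated-measures ANOVA and then paired t-tests at p < 0.05, with no multiplicity adjustment stated.

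**The concern.** The Friedman test ranks the three feet within each subject. Its standard statistic allows for ties: when many subjects score the same on two or three feet, the rank variance shrinks and the test adjusts. The usual Dunn comparison after Friedman does not adjust. It divides the rank-sum difference by a standard error fixed by the number of subjects and conditions, whatever the ties. The omnibus test and the post hoc test then use different yardsticks, and the post hoc one is too long. The other form of Dunn's test, for independent groups, discards the pairing altogether.

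Ties are plausible here: the ratings are ordinal, each subject is his or her own control, and all subjects have been trained to a minimum standard on every foot.

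What is at stake is the pairwise answer. Hypothesis 1.1 claims an advantage of two foot types over the third, particularly on inclines and declines, and the study aims at prescription criteria. A significant omnibus p-value with no pair identified does not serve that aim.

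**Working it through.** **The plan's own power figure.** *Power Analysis* reads "Assuming an alpha error rate of 5% and within-group standard deviation of 5", and "120 subjects will provide over 98% power to detect a 3 unit difference" between at least two groups. Assume two-sided alpha, means 0, 1.5 and 3, and zero within-subject correlation.
- Repeated-measures F: noncentrality 120 × (1.5² + 0² + 1.5²)/5² = 120 × 4.5/25 = 21.6 on 2 and 238 df, power 99.0%.
- Bonferroni-adjusted paired t for the extreme pair: 3/(5√2) × √120 = 4.65 on 119 df, power 98.6%.

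The stated figure reproduces, but it concerns an ANOVA. No power is given for Friedman or Dunn.

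**Critical values, n = 120, k = 3.** Let c be the ratio of actual to no-tie rank variance, and D the largest rank-sum difference. The Friedman statistic is assumed tie-corrected, as is standard.
- Friedman-form Dunn: z = D/√(nk(k+1)/6) = D/√240. The Bonferroni cut for three pairs is 2.394, so D must exceed 2.394 × √240 = 37.1 whatever c is.
- Tie-corrected form: 2.394 × √(240c). At c = 0.5 this is 26.2.
- Friedman, feet evenly spaced: deviations −D/2, 0, D/2, so the statistic is (1/120) × (D²/2)/c = D²/(240c). Against 5.991 it is significant from D = 37.9 at c = 1 and from 26.8 at c = 0.5.
- Friedman, one foot shifted: deviations 2D/3, −D/3, −D/3, so the statistic is D²/(180c), significant from 32.8 at c = 1 and from 23.2 at c = 0.5.

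At c = 0.5, evenly spaced feet with D between 26.8 and 37.1 give a significant Friedman test and no flagged pair. Without ties that gap does not exist. With one foot shifted, a small gap (32.8 to 37.1) exists even without ties; that is the ordinary cost of the Bonferroni step. Ties widen it to 23.2 to 37.1, and tie correction brings it back to 23.2 to 26.2.

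**Simulation.** Latent normal ratings were cut into levels, with 120 subjects on three feet. Number of levels, within-subject correlation and effect are assumptions. The entries are the share of significant Friedman tests with no pair flagged, for one foot better by 0.2 latent SD and equally likely levels (2,000 runs per setting):

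| Levels, correlation | Tied on all three feet | No-tie variance | Tie-corrected |
|---|---|---|---|
| no ties, 0.8 | 0% | 4% | 4% |
| 12, 0.8 | 9% | 13% | 2% |
| 6, 0.8 | 22% | 32% | 3% |
| 4, 0.8 | 35% | 55% | 4% |
| 3, 0.95 | 69% | 89% | 1% |

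In the four tied settings the no-tie figures become 1, 4, 15 and 28% at a 0.3 SD shift, and 42, 67, 86 and 99.9% at 0.1 SD. The tie-corrected form misses 0 to 11%. The independent-groups form misses 45 to 69% at 0.3 SD and over 90% at 0.2 SD or less.

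A separate run with five levels, a 0.25 SD shift and correlation 0.6 to 0.8 gave 22 to 83% with the no-tie variance, 1 to 5% tie-corrected, and 1 to 16% for Holm-adjusted Wilcoxon tests. With 12 levels the no-tie figure was 5 to 14%. A third run (five levels, 0.25 SD, correlation 0.6 to 0.9) varied the share of ratings in the top level: 5 to 30% missed with 20% at the top, 37 to 60% with 50%, and 92 to 94% with 70%.

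**False positives.** With no true difference, the per-pair false-positive rate was 0 to 0.3% for Dunn and 1 to 2% for Holm-adjusted Wilcoxon after the Friedman gate.

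**The case against.** Four counter-arguments have weight.

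1. *The paired form is the natural reading.* Dunn is named in the same sentence as a repeated-measures Friedman test. A reader might infer that the plan ignores pairing; the wording allows that but does not show it. The independent-groups figures are therefore not the main case.

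2. *Tie handling may sit in an SAP that is not shown.* Nothing in the protocol excludes a tie-corrected variance, and a tie-corrected version of the same comparison would be acceptable. This stands in part. Still, the protocol names a particular test, and its usual form has the defect; the point challenges a stated choice.

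3. *The same ratings are tested again under Hypothesis 1.2.* A reader might infer that the trial could not say which foot is better on stairs or hills. The protocol does not support that: the ANOVA and paired t-tests compare the same three feet and could detect a pair that Dunn misses. But they treat ordinal ratings as interval data, state no adjustment, and could contradict the Hypothesis 1.1 result.

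4. *The tie rate is unknown.* A reader might infer from the training standard that ratings cluster at the top. That standard is a floor on a different instrument. It makes equal ratings plausible but shows no ceiling on SAI or HAI.

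The error also runs in the conservative direction, with no inflation of false positives.

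**Conclusion.** The point holds in a limited form. For tied paired ratings, the usual Friedman-form Dunn test is stricter than it needs to be, and the Hypothesis 1.1 analysis can end with a significant Friedman test and no foot pair identified. An unconditional statement that differences would often be missed is not supported, because the protocol gives neither tie rate nor effect. Under assumed five-level scales and a 0.25 SD shift, about 20 to 80% of significant Friedman tests flag no pair, and more if most ratings sit in the top level. With 12 levels it is about 5 to 14%. Without ties only the ordinary multiplicity cost remains. The cause is the variance: correcting it for ties removes most of the loss in every tied setting examined. The loss is confined to Hypothesis 1.1. The change is worth making because it is almost free and the pairwise result is what that hypothesis needs.

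**What to change.** Under Hypothesis 1.1, replace the Dunn test with a paired, tie-aware comparison of the three foot pairs after the Friedman test. Either of these would do:

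- Wilcoxon signed-rank tests, Holm-adjusted over the three pairs, with zero differences dropped; or
- Friedman rank-sum comparisons with tie-corrected variance and a stated multiplicity adjustment.

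The second stays closer to the named method and does not rank the sizes of differences between ordinal levels, which the signed-rank test does. For each pair, also report the share of subjects rated better, equal and worse, so that the tie rate is visible.

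The cost is one sentence of wording and a slightly less conservative pairwise test. No extra data or subjects are needed.
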